### Adverse events

2.6.

Determination of intervention-related adverse events will be made, and procedure modifications executed, if needed. If modifications cannot be made, the study will be terminated. Risks related to suicidality, dangerous alcohol use, and withdrawal symptoms will be assessed at every visit. Withdrawal symptoms will be measured using the Sweating, Hallucinations, Orientation, Tremor (SHOT) scale, with adaptations for virtual evaluation [33]. If a participant scores >3 on the SHOT, we will administer the Clinical Institute Withdrawal Assessment for Alcohol to determine if immediate medical intervention is needed [33].

## Analytic plan

3.

### Preliminary analyses

3.1.

Our data and supporting documents will be submitted to the National Institute on Alcohol Abuse and Alcoholism’s National Data Archive (NDA) and will be available within three years of completion of the study. Groups will be compared for differences in demographics and pre-treatment alcohol use. Means and standard deviations will characterize continuous variables, and percentages and frequencies characterize categorical variables. We will assess the impact of sex as a biological variable. Our alpha threshold for statistical significance will be 0.05.

### Treatment efficacy

3.2.

We will follow an intention-to-treat approach to provide unbiased group comparisons. Treatment efficacy will be assessed per our primary outcome, PEth-defined abstinence. In the Starting Phase, abstinence will be defined as a week-over-week decrease in PEth levels (yes/no). During the Sustaining Phase and Follow-up Phase, abstinence will be defined as PEth <20 ng/mL (yes/no). Separate generalized estimating equations (GEE) with logit link functions will be used to assess abstinence during treatment (11 assessments across 26 weeks) and follow-up (4 assessments across 52 weeks). The frequency of PEth-defined excessive drinking (≥200 ng/mL; yes/no) will also be analyzed with GEE. GEEs with appropriate link functions will also assess additional outcomes for the longest duration of PEth-defined abstinence, uEtG results (positive/negative), self-reported days of drinking, self-reported drinks per day, and alcohol-associated harms (cigarette smoking, drug use, utilization of costly medical care). All GEE models will include effects for groups, biological sex, time, and the group-by-time interaction. Statistically significant group-by-time interactions will be evaluated with Bonferroni corrected post hoc tests.

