We previously conducted a pilot study for a telehealth-based CM model that used the blood biomarker phosphatidylethanol (PEth) to assess alcohol consumption [7]. The PEth homologue 16:0/18:1 can be detected for up to 28 days [8], thus assessing abstinence or low levels of drinking can occur as infrequently as once a month. Accordingly, our pilot study (*n* = 16) used a two-phase CM treatment approach. Phase 1 helped participants initiate abstinence with weekly PEth assessment and reinforcement of week-to-week decreases in PEth levels. Once PEth levels indicated sustained reductions in alcohol consumption (PEth <20 ng/mL), participants transitioned to Phase 2 where sampling and reinforcement decreased to once every two to four weeks. By reducing sample frequency, we were able to extend the CM intervention duration to 26 weeks. Participants reported high satisfaction with study procedures, to include self-collection of blood samples using the TASSO-M20 device, suggesting that our telehealth-based model was feasible. Additionally, CM participants were five times more likely than Control participants to submit PEth samples indicative of alcohol abstinence (*p* = 0.007), indicating that our telehealth-based CM model was also efficacious [7].

Based on these pilot results, we received funding to conduct a randomized controlled clinical trial of our telehealth-based CM intervention for AUD (R01AA031013; ClinicalTrials.gov ID NCT06265506). For this study, our primary aim is to determine whether the frequency of PEth-defined abstinence (<20 ng/mL) or absence of regular excessive drinking (<200 ng/mL) is higher in those receiving CM compared to the Control group during the intervention and follow-up periods. Additional aims include a) assessing group differences in alcohol-associated harms, (e.g., cigarette/tobacco use, drug use, costly medical care), b) describing the association between the Addictions Neuroclinical Assessment (ANA) framework variables (incentive salience, executive functioning, negative emotions) and alcohol outcomes [9], and c) conducting a cost-effectiveness analysis to determine the value of the CM group relative to the Control group, from the healthcare sector, state policymaker, and societal perspectives.

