#### CM group

2.3.2.

Participants will receive CBT4CBT in addition to their reinforcers being contingent on PEth results. The criteria for PEth-verified abstinence will differ depending on the treatment phase. During the Starting Phase, week-over-week decreases in PEth levels, regardless of the amount, will be reinforced until participants reach PEth <20 ng/mL, which is consistent with approximately four weeks of abstinence. After completing 4 weeks of the Starting Phase and/or achieving PEth <20 ng/mL, participants will transition to the Sustaining Phase with visits every two to four weeks, as long as abstinence is maintained. Should PEth levels indicate that drinking occurred since the last visit (≥20 ng/mL), CM participants will return to the Starting Phase with weekly visits until PEth levels once again indicate abstinence (see Fig. 2). Returning to the Starting Phase provides CM participants with additional support when a drinking episode occurs. Participants will continue the Sustaining Phase when their PEth levels return to abstinence (<20 ng/mL), and treatment duration will remain 26 weeks regardless of how long a participant remains in the Starting Phase or how many times they return to the Starting Phase.

During the Starting Phase, participants will receive $20 for the first PEth result that indicates reduced alcohol consumption (i.e., week-to-week decrease). They will then receive an additional $5 for every week of consecutive abstinence (i.e., week-to-week decrease during the Starting Phase, <20 ng/mL during the Sustaining Phase). PEth-positive samples (i.e., week-to-week PEth increase, PEth ≥20 ng/mL) will result in reinforcers being withheld until the next negative test, for which the participant will earn $20. A subsequent negative test will then reinstate the total reinforcers earned prior to testing positive, plus an additional $5. For example, if a participant previously earned $40 but then tests positive, they will receive $0 at the current visit. When the participant submits the next negative sample, they will earn $20, and then be eligible for reinstating their highest earned total (e.g., $40) plus an additional $5 when they have two consecutively negative samples. This reinforcer escalation schedule, reset, recovery approach is consistent with previous CM studies [21,22].

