#### Control group

2.3.3.

Participants will receive CBT4CBT with their reinforcers contingent on submitting blood samples, not PEth results. Blood sample collection will occur on a fixed schedule of once weekly (Weeks 1-4), then every other week (Weeks 6 and 8), followed by every four weeks (Weeks 12, 16, 20, and 24), and a last intervention visit occurring on Week 26 (see Fig. 1). Similar to previous studies, the amount of reinforcement allotted for each sample will be a base level of $20 or yoked to the CM group [23,24]. When Control participants submit a blood sample, they will receive a reinforcer amount that is equal to the average provided to CM participants during the previous month, resulting in earnings that approximate the CM group. For example, if the average earning per sample in the CM group was $50, Control participants will receive $50 for each sample submitted. Total Control group reinforcement could be as high as $1,820 but is expected to be 50% of that amount.

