#### PEth sample collection and analyses

2.5.1.

Staff will mail study kits to participant residences. The kit will include a TASSO-M20 device for blood collection, isopropanol swabs, towelettes, a bandage, a urine cup, a uEtG dipcard, and a pre-paid shipping envelope. The TASSO-M20 device will be pre-labeled with the participant study ID and the visit number. Participants will self-collect blood from the upper arm with the TASSO-M20 device while videoconferencing with staff. Participants will press a button on the device to create a small lance in the skin, from which capillary blood will fill four plugs in the device (20 μL ± 5%/plug) over the span of five minutes (see tassoinc.com). Once completed, participants will remove the device, take the film cover over the plugs off to allow air drying, and seal the device in a prepaid FedEx envelope. Participants will mail the packet to the University of Texas Health San Antonio for PEth analysis. Our pilot study demonstrated that the TASSO-M20 device is a feasible method for collecting blood, e.g., consistency of blood volume collected, easy for participants to use, minimal pain [7].

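### The primary outcome scores any PEth fall in the Starting Phase as abstinence, so a participant with flat PEth passes about half of those visits by chance, and the plan does not say whether Control samples are scored this way

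*Protocol article*

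**What the plan says.** Section 3.2 (Treatment efficacy) gives the primary outcome two definitions. For early treatment: "In the Starting Phase, abstinence will be defined as a week-over-week decrease in PEth levels (yes/no". Afterwards: "During the Sustaining Phase and Follow-up Phase, abstinence will be defined as PEth <20 ng/mL (yes/no". Neither sentence sets a minimum fall for the first rule. Section 2.3.2 (CM group) states the matching reinforcement rule, and there the absence of a threshold is explicit: "week-over-week decreases in PEth levels, regardless of the amount, will be reinforced".

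Elsewhere abstinence is a level, not a change. The Introduction states the primary aim as "whether the frequency of PEth-defined abstinence (<20 ng/mL) or absence of regular excessive drinking (<200 ng/mL) is higher", and Table 1 lists PEth-defined abstinence only as below 20 ng/mL. The Abstract calls the primary outcome PEth-negative tests, having set positive at 20 ng/mL or more for entry.

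The phases are described for one arm only. Under Section 2.3.2, after a sample at or above 20 ng/mL, "CM participants will return to the Starting Phase with weekly visits until PEth levels once again indicate abstinence". Section 2.3.3 (Control group) names no phases: "Blood sample collection will occur on a fixed schedule of once weekly (Weeks 1-4), then every other week (Weeks 6 and 8", then Weeks 12, 16, 20, 24 and 26. That makes 4 + 2 + 5 = 11 samples, matching the 11 treatment assessments in Section 3.2. No section says which rule scores Control samples in Weeks 1-4.

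**The concern.** A yes/no outcome that turns on the sign of a difference between two noisy readings has a high chance success rate when nothing has changed. Better assay precision does not help, because any non-zero difference counts. Two consequences follow.

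- **Meaning.** Participants whose drinking has not changed will often be reported as having PEth-defined abstinence, which is not the below-20 outcome named in the primary aim.
- **The comparison.** If both arms are scored by this rule, chance successes pull the odds ratio toward 1. If only CM is, they are credited to CM alone. The text leaves both open, so the direction of the error is not fixed.

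Section 3.2 also analyses longest duration of abstinence, and Section 3.3.1 uses in-treatment abstinence as a predictor of follow-up. Both would inherit the same misclassification.

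**Working it through.** **Inputs from the article.** No minimum fall (Section 3.2); 11 treatment assessments, of which 4 are weekly (Sections 2.3.3 and 3.2); entry PEth at least 20 ng/mL (Section 2.2.1); sample volume tolerance in "capillary blood will fill four plugs in the device (20 μL ± 5%/plug" (Section 2.5.1). No assay CV and no reporting precision are given. The plan states no misclassification rate, so there is no figure of its own to reproduce here.

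**Step 1: chance rate per visit.** Let true PEth be flat and the errors exchangeable and continuous. Then P(this reading < last reading) = 1/2 by symmetry, whatever the error size. A simulation of 200,000 participants, with assumed CVs of 2% to 30% and assumed median PEth of 30, 100 and 200 ng/mL, gave 0.498 to 0.503 at Weeks 1-4. Autocorrelated variation around a stable mean (correlation 0 to 0.9) also gave 0.50. If results are rounded to whole ng/mL, ties lower the rate:

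| Assumed median PEth | CV 5% | Over CVs of 2% to 30% |
|---|---|---|
| 100-200 ng/mL | 0.46-0.48 | 0.41-0.50 |
| 30 ng/mL | about 0.42 | 0.31-0.49 |

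A true rise of 5% per week would still be scored abstinent 25% of the time at CV 5% and 45% at CV 30%.

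**Step 2: share of the treatment period.** For a participant with flat PEth well above 20 ng/mL:

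- decrease rule in Weeks 1-4 only: 4 × 0.5 / 11 = 18%;
- decrease rule at all 11 (upper bound, possible only for CM through re-entry): 11 × 0.5 / 11 = 50%;
- decrease rule never applied (one reading for Control): 0%.

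**Step 3: both arms scored by the rule in Weeks 1-4.** Illustrative model: a share q is truly abstinent and always scored so; the rest are flat and above 20 ng/mL. Then p(Weeks 1-4) = q + 0.5(1 − q), and p(11 assessments) = q + (4/11) × 0.5(1 − q).

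| q, CM vs Control | True OR | Weeks 1-4 | OR | All 11 | OR |
|---|---|---|---|---|---|
| 43% vs 20% | 3.02 | 71.5% vs 60.0% | 1.67 | 53.4% vs 34.5% | 2.17 |
| 30% vs 10% | 3.86 | 65.0% vs 55.0% | 1.52 | 42.7% vs 26.4% | 2.08 |

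Within Weeks 1-4 alone, a true OR of 1.7 becomes 1.07 to 1.23 for assumed Control rates of 5% to 20%.

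**Step 4: the arms scored by different rules, with no true effect.** Let a share f of each arm be flat drinkers, and the rest abstinent at half of visits. Expected scored rates are 0.5(1 − f) with no decrease rule, 0.5(1 − f) + (2/11)f with it in Weeks 1-4, and 0.5 with it throughout.

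| f | CM Weeks 1-4, Control never | False OR | CM throughout, Control Weeks 1-4 | False OR |
|---|---|---|---|---|
| 0.3 | 40.5% vs 35.0% | 1.26 | 50.0% vs 40.5% | 1.47 |
| 0.5 | 34.1% vs 25.0% | 1.55 | 50.0% vs 34.1% | 1.93 |
| 0.7 | 27.7% vs 15.0% | 2.17 | 50.0% vs 27.7% | 2.61 |

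These show direction and possible size; f is assumed.

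**Step 5: what a margin can do.** A repeatability limit is 2.77 × CV. If all the variation is analytical, it cuts false falls from about 50% to about 2.5%. Section 2.3.2 links a level below 20 ng/mL to roughly four weeks of abstinence. Read as a constant proportional fall, the weekly fall from a start S is 1 − (20/S)^(1/4): 44% from 200, 20.5% from 50, 9.6% from 30. An abstinent participant misses the margin m until below 20 ng/mL if S < 20/(1 − m)^4.

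| Assumed CV | Margin | Missed if start is below about |
|---|---|---|
| 5% | 13.9% | 36 ng/mL |
| 10% | 27.7% | 73 ng/mL |
| 15% | 41.6% | 171 ng/mL |

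A margin is therefore useful, but it must be kept small relative to low entry levels.

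**The case against.** The best defence is that the rule is deliberate. PEth clears slowly, and the Introduction puts detection at up to 28 days, so a strict below-20 rule would miss participants who stop drinking at enrolment. That stands, and it is why the fix keeps credit for falls in Weeks 1-4. It does not justify counting a fall of any size. Some falls in a stable drinker also reflect real variation in drinking, and Section 2.3.2 means to reward reduced consumption. That is a reason to reinforce such a fall, not to call it abstinence in the efficacy analysis. The group-by-time term may reveal a different early effect, but it does not remove the misclassification.

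A reader might infer more than the article supports:

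- **That both arms are affected equally.** The phase is described for CM only. One definition within an intention-to-treat analysis makes common scoring in Weeks 1-4 a natural reading, but no sentence says so.
- **That half of all treatment results are spurious.** One half is per Starting Phase visit; the Weeks 1-4 odds ratios are likewise not those of the 11-assessment contrast.
- **That measurement noise alone is responsible.** The article gives a volume tolerance but no assay CV, and the symmetry argument covers ordinary variation too.
- **That the power calculation fails because Control cannot score 0%.** Section 3.5 uses the pilot's 43% vs 0% for one illustration, then plans on odds ratios of 1.7 and 1.34. It does not say how the pilot rates were scored.

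**Conclusion.** The concern holds in this limited form. The stated rule gives a participant with flat PEth about an even chance of being scored abstinent at each Starting Phase visit, and it differs from the below-20 definition in the primary aim and Table 1. The one-half needs only flat true PEth, exchangeable errors and few ties. The effect on the trial result depends on a choice the article does not state. Common scoring in Weeks 1-4 dilutes the effect, moderately over 11 assessments (3.0 to about 2.2 in the illustration). Scoring by phase, which only CM has and can re-enter, biases toward CM. The odds ratios rest on assumed shares and are not predictions. Follow-up, scored below 20 ng/mL, is not affected directly. This should be settled before outcome data are examined by arm.

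**What to change.** Change the efficacy scoring only; the reinforcement rule is outside this point.

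1. Score Weeks 1-4 by calendar week, identically in both arms. Count a sample as abstinent if PEth is below 20 ng/mL or has fallen by more than an analytical repeatability margin.
2. Fix that margin before unblinding, from laboratory QC or duplicate-plug data. Such data give analytical variation, not within-person variation, so they will not remove every chance fall.
3. Set the margin below the weekly fall expected under full abstinence at low entry PEth, and show results over a range of margins, since the article gives no assay CV.
4. Use below 20 ng/mL for both arms at all later treatment assessments, whatever phase a CM participant is in.
5. Report two sensitivity analyses: any decrease in Weeks 1-4, and below 20 ng/mL at every visit.
6. Bring the Introduction, Section 3.2 and Table 1 into line with the chosen definition.

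The cost is revised wording, one constant and two further model runs, with no new samples. The downside is that some small true reductions, and some slow falls in abstinent participants with low starting PEth, will not be counted in Weeks 1-4.

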If CM participants have an unexcused missed visit or do not ship their sample within a week of the study visit, the PEth sample will be considered positive. In such cases, reinforcers will be withheld, and the participant will return to the Starting Phase. The maximum CM reinforcer that can be earned per week of abstinence is $90 (e.g., for visits occurring once every 4 weeks the max is $360). The maximum total amount that can be earned for negative PEth results during the CM intervention is $1,820.

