## Discussion

4.

This randomized controlled clinical trial assesses the efficacy of a telehealth-based CM intervention for AUD in a large national sample. Telehealth delivery has some potential limitations, such as access to and comfort with technology, but advantages, like reduced stigma and travel, likely outweigh the disadvantages. For instance, 64% of participants in our telehealth-based CM pilot study were treatment-naïve [7], suggesting that telehealth interventions might be a low-burden and low-barrier treatment option for individuals with AUD.

While CM is an evidence-based treatment for AUD and a powerful tool for initiating abstinence, evidence for sustained post-intervention effects is less conclusive [23,47,48,52,56]. In efforts to address this gap in CM research, the follow-up period for this study is 12 months in duration compared to 6 months in traditional CM models. Another strength of this study is the utilization of the ANA framework and alcohol biomarkers to identify potential predictors of treatment response and long-term outcomes. These predictors could provide opportunities to improve treatment efficacy and better direct care for this population (e.g., individualized treatment approaches). Lastly, this study will fill a critical gap in the CM literature by providing essential information for providers regarding resource and cost requirements for implementing this telehealth-based CM model.

A limitation of the study is that there is up to a one-week delay between submission of blood samples and provision of CM reinforcers. If we do not observe an effect of CM on outcomes, it could be a result of this delay. However, in our pilot study, CM participants did not report concerns regarding the week delay (i.e., surveys and qualitative interview) and achieved levels of alcohol abstinence consistent with previous CM studies [7]. Another potential limitation is the increased burden for the CM group, depending on how long participants remain in the Starting Phase. More visits might contribute to higher attrition in the CM condition, or it could lead to lower levels of attrition because individuals who are unable to achieve long-term abstinence (i.e., <20 ng/mL) will have more frequent visits and a lower bar for achieving reinforcers. The effects of an adaptive reinforcement schedule on attrition rates in the CM group will be assessed.

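### Primary abstinence is scored by treatment phase, and only CM participants can return to the phase where any weekly fall in PEth counts as abstinent

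*Protocol article*

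**What the plan says.** Section 3.2 defines the primary outcome in two parts: "In the Starting Phase, abstinence will be defined as a week-over-week decrease in PEth levels (yes/no"), and "During the Sustaining Phase and Follow-up Phase, abstinence will be defined as PEth <20 ng/mL (yes/no"). The scores from both arms enter one logit GEE to "assess abstinence during treatment (11 assessments across 26 weeks").

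The phases are defined in Section 2.3.2, under the CM group: "The criteria for PEth-verified abstinence will differ depending on the treatment phase". In the Starting Phase a fall of any size counts. After a result ≥20 ng/mL, "CM participants will return to the Starting Phase with weekly visits until PEth levels once again indicate abstinence". An unexcused missed visit or an unshipped sample is treated as positive: "In such cases, reinforcers will be withheld, and the participant will return to the Starting Phase". The Fig. 2 legend repeats the return rule for results ≥20 ng/mL.

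Section 2.3.3 gives Control no phase and no return: "Blood sample collection will occur on a fixed schedule of once weekly (Weeks 1-4), then every other week (Weeks 6 and 8"), then Weeks 12, 16, 20, 24 and 26. The aim in the Introduction and the entry in Table 1 both give abstinence as <20 ng/mL, with no phase rule.

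**The concern.** The rule that decides what counts as abstinent is set by the intervention's own visit algorithm, and that algorithm operates in one arm. After Week 4, a CM participant who is still drinking goes back to the looser rule. A Control participant with the same PEth values does not. Control samples are then two to four weeks apart, so a weekly fall could not be scored for Control in any case.

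The Discussion recognises the looser rule, though only for payment: "individuals who are unable to achieve long-term abstinence (i.e., <20 ng/mL) will have more frequent visits and a lower bar for achieving reinforcers". Section 3.2 carries the same criteria into the primary outcome.

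Two things are at stake. The primary in-treatment comparison can favour CM when the arms drink alike. And one CM sample can be abstinent on the primary outcome while meeting the secondary definition of excessive drinking (≥200 ng/mL).

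**Working it through.** **1. Assessment count.** From Section 2.3.3: Weeks 1–4 (4) + Weeks 6 and 8 (2) + Weeks 12, 16, 20 and 24 (4) + Week 26 (1) = 11. This reproduces the figure in Section 3.2. Seven of the 11 fall after Week 4.

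**2. How many the looser rule can reach.** Suppose a CM participant first leaves the Starting Phase at Week 4 or at the first result <20 ng/mL, whichever comes first. Someone who stays ≥20 is then scored by the strict rule at Week 6, fails, and returns to weekly visits. Weeks 8, 12, 16, 20, 24 and 26 are open to decrease scoring: 6 of 11. If the first exit requires <20 ng/mL, Week 6 is added: 7 of 11.

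**3. One path.** Take PEth of 400 ng/mL every week, except 390 at Weeks 8, 12, 16, 20, 24 and 26. There is no net decline, and each dip is a fall from the week before. CM scores 6 of 11 abstinent. Control, scored by calendar (decrease at Weeks 1–4, <20 afterwards), scores 0 of 11. All six CM successes are ≥200 ng/mL. This path is built to show the maximum.

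**4. Pooled effect with no treatment effect.** PEth is the same in both arms, Control is scored by calendar, and the first exit is whichever comes first. The inputs are assumptions:
- p = share truly <20 ng/mL at Weeks 6–26
- d = share scored abstinent at Weeks 1–4, equal in both arms
- q = chance that a CM sample ≥20 ng/mL at Weeks 8–26 is a fall from the prior week

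Control = (4d + 7p)/11

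CM = Control + 6(1 − p)q/11

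With p = 0.3 and d = 0.5, Control = (2.0 + 2.1)/11 = 0.373. At q = 0.1, CM = 0.373 + 6 × 0.7 × 0.1/11 = 0.411, so OR = (0.411/0.589)/(0.373/0.627) = 1.17.

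| q | CM share (p = 0.3, d = 0.5) | OR | OR range, p = 0.1–0.5, d = 0.3–0.7 |
|---|---|---|---|
| 0.10 | 0.411 | 1.17 | 1.12–1.37 |
| 0.25 | 0.468 | 1.48 | 1.32–2.01 |
| 0.50 | 0.564 | 2.17 | 1.73–3.44 |

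In this example the OR reaches 1.34 at q of about 0.185 and 1.7 at q of about 0.34. PEth that fluctuates without trend falls about half the time, which is q = 0.5. With 7 open assessments instead of 6, the ranges become 1.14–1.43, 1.38–2.21 and 1.90–4.07.

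The formula is an upper case for its inputs. It treats every CM sample ≥20 ng/mL at Weeks 8–26 as taken when the participant is already back in the Starting Phase. In fact the first such result after a spell <20 is still scored not abstinent.

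**5. Simulations.** Both have no treatment effect and assumed PEth values.
- *First.* Median baseline 250 ng/mL, within-person SD of log PEth 0.3 or 0.5, lag-1 correlation 0.5 or 0.8, responders' half-life 7 days, 60,000 paths per scenario, each scored under both arms' rules. The OR was 2.43–2.44, 1.96–1.98 and 1.70–1.73 with 20%, 40% and 60% responders.
- *Second.* Median 80 ng/mL, log-SD 1.2 between and 0.5 within persons, about 14% of samples <20 ng/mL, 75 per arm, 300 runs, independence GEE. This one lets the first result ≥20 in the Sustaining Phase fail. The phase rule gave 51% abstinent in CM against 29% in Control, OR about 2.6, and rejection in every run. Decrease scoring at Weeks 1–4 and <20 afterwards, in both arms, gave OR 1.00 and 8% rejection. Scoring <20 at all 11 visits gave OR 1.03 and 4%.

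**The case against.** The best defence is that Section 3.2 uses the phases as calendar periods in both arms: Starting for Weeks 1–4, Sustaining for the rest of treatment. Several points lean that way. The outcome is stated once, for a two-arm model with 11 assessments, which is the fixed calendar count. Section 2.4 uses the phase names for visit lengths without naming an arm. The Follow-up Phase, listed alongside the other two, is a calendar period. A status-based phase would leave Control with no in-treatment definition, which is unlikely to be intended. Figs. 1 and 2 are not available here and might label phases for both arms. Under this reading the artefact is nil.

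That intent is possible, but the available text does not state it. Section 2.3.2 and the Fig. 2 legend tie the phase to the participant's own PEth. Nor do eleven shared visits say which definition applies to a CM participant who is back in the Starting Phase at Week 12.

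Other objections stand in part. The size rests on assumed inputs, so no single odds ratio is the expected bias. Counting missed CM samples as positive, with no such rule stated for Control, would work against CM if carried into scoring; the calculations do not include it. Follow-up abstinence and the ≥200 ng/mL outcome use one threshold in both arms and are untouched.

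**Conclusion.** The point holds as written. Following Sections 3.2 and 2.3.2 literally applies a looser definition of abstinence after Week 4 in the CM arm only, contrary to the <20 ng/mL aim. The logical maximum for a participant who stays ≥20 ng/mL is 6 of 11 assessments. With no true effect, the artefact ranges from small (OR 1.12) to well above the planned effect (OR 3.44), depending mainly on how often CM samples that remain ≥20 ng/mL are weekly falls. Both simulations reach or exceed 1.7, the smallest effect the plan expects. These sizes depend on assumed PEth behaviour and on the phase following the participant's status in CM. Only the in-treatment comparison is affected. Confidence is medium, because the sponsor may intend the calendar reading.

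**What to change.** In Section 3.2, define in-treatment abstinence by study week, identically in both arms and regardless of CM phase:
- **Weeks 1–4:** a decrease from the previous sample, or already <20 ng/mL.
- **Weeks 6, 8, 12, 16, 20, 24 and 26:** PEth <20 ng/mL.

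State that the extra weekly CM samples decide payment only.

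This removes the asymmetry between arms. A sample at Weeks 1–4 could still be both abstinent and ≥200 ng/mL, but equally in each arm. Scoring <20 ng/mL at all 11 visits would remove that too and match the stated aim directly.

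The change is wording only and needs no new data. CM abstinence may look less favourable, possibly by a material amount. Some fully abstinent participants with slow clearance would be scored not abstinent at Week 6, in either arm alike. Over 25 assumed clearance paths (baseline 50–800 ng/mL, half-life 4–12 days), 5 are still ≥20 ng/mL at Week 6, for example 400 × 0.5^(42/10) = 21.8. One is at Week 8: 800 × 0.5^(56/12) = 31.5.

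As a minor tidy-up, Section 2.3.2 and the Fig. 2 legend could give the first exit as Week 4 or the first result <20 ng/mL, whichever comes first.

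### The 11 treatment assessments in the GEE match the fixed Control calendar, but CM sampling follows the PEth result and is not tied to those weeks

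*Protocol article*

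**What the plan says.** Section 3.2 specifies a GEE for "abstinence during treatment (11 assessments across 26 weeks", with terms for group, sex, time and group-by-time. Section 3.5 bases power on the same 11 assessments. Neither section names an arm or says which CM samples are analysed.

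For Control, Section 2.3.3 states: "Blood sample collection will occur on a fixed schedule of once weekly (Weeks 1-4), then every other week (Weeks 6 and 8", then "followed by every four weeks (Weeks 12, 16, 20, and 24), and a last intervention visit occurring on Week 26".

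For CM, Section 2.3.2 says participants "transition to the Sustaining Phase with visits every two to four weeks, as long as abstinence is maintained". After a PEth of 20 ng/mL or more, "CM participants will return to the Starting Phase with weekly visits until PEth levels once again indicate abstinence". An unexcused missed visit or an unshipped sample also returns them to the Starting Phase.

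Section 2.4 has blood and urine collected at each visit, and Table 1 lists PEth and uEtG under every visit, so the number of samples follows the number of visits. The Discussion recognises that "individuals who are unable to achieve long-term abstinence (i.e., <20 ng/mL) will have more frequent visits", but treats this only as a matter of burden and attrition.

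**The concern.** In one arm only, the last PEth result decides how often, and in which weeks, the outcome is next measured. A GEE with independence working correlation gives each sample equal weight, so CM participants who keep drinking count for more than those who stop. An exchangeable structure reduces this but does not remove it.

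There are two obvious ways to build the data set, and the article does not choose between them. Using every sample over-represents CM drinkers. Keeping only CM samples taken in Control weeks is sound if CM visits are scheduled there. It can again over-represent drinkers if abstainers' visits have moved to other weeks.

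This affects the primary comparison and the other biomarker outcomes drawn from the same visits. It is also a matter of conduct: a Week 12 sample that was never drawn cannot be supplied later by an analysis plan.

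**Working it through.** **1. The plan's figure.** Control visits: 4 (Weeks 1–4) + 2 (Weeks 6, 8) + 4 (Weeks 12, 16, 20, 24) + 1 (Week 26) = 11. This reproduces the stated number.

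**2. The CM count.** Weekly visits throughout give at most 26. For a participant abstinent from Week 4 on, four-weekly visits give Weeks 1–4 plus 8, 12, 16, 20 and 24, which is 9. The Control spacing gives 11. Even two-weekly visits throughout would give 4 + 22/2 = 15.

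**3. Weighting by hand.** Assume 40% of CM participants are abstinent throughout with 11 samples each, and 60% never reach <20 with 26 samples each. The pooled share of samples <20 is 0.4×11 / (0.4×11 + 0.6×26) = 4.4/20 = 22%, although 40% of participants are abstinent. This is a crude proportion, not a GEE estimate, but it shows the mechanism.

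**4. Simulation with no group difference.** All inputs here are assumptions, not figures from the article:
- 100 per arm, with the same weekly log-PEth process in both arms: between-person SD 1.3, within-person SD 0.8, autocorrelation 0.7.
- Median PEth 40 or 120 ng/mL; 200 replicates each.
- CM seen weekly while ≥20, otherwise only in Control weeks.
- Logit GEE with group and linear time, robust standard errors, alpha 0.05.

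CM participants gave a mean of 20.5 (median 40) or 23.9 (median 120) samples, against 11 in Control. The true odds ratio (CM:Control) is 1.

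| Outcome and samples used | Working correlation | OR, median 40 / 120 | Null trials rejected |
|---|---|---|---|
| <20, all samples | independence | 0.56 / 0.58 | 70% / 39% |
| <20, all samples | exchangeable | 0.87 / 0.84 | 13% / 10% |
| <20, 11 common weeks | either | 1.00 / 0.99 | 7% / 3–4% |
| ≥200, all samples | independence | 1.33 / 1.14 | 18% / 10% |
| ≥200, all samples | exchangeable | 1.05 / 1.01 | 5% / 6% |
| ≥200, 11 common weeks | either | 1.02 / 0.99 | 5–7% |

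For <20, an OR below 1 goes against CM; for ≥200, an OR above 1 does. With 200 replicates, the Monte Carlo standard error around 5% is √(0.05×0.95/200) = 1.5 percentage points, so the common-week rejection rates are compatible with 5%.

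A repeat null simulation gave 0.55–0.59 (37–75% rejected) with independence and 0.84–0.88 (8–17%) with exchangeable for <20 on all samples. It gave 0.98–1.00 (2–5%) on common weeks, and 1.15–1.36 for ≥200 on all samples.

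**5. Control weeks only, with drifting CM visits.** The Fig. 2 caption returns participants to monthly visits after a relapse. Someone who clears at Week 9 and is then seen every four weeks comes at Weeks 13, 17, 21 and 25, and misses Weeks 12, 16, 20 and 24. With CM visits drifting in this way, restriction to Control weeks gave an OR of 0.49–0.53 under one spacing assumption and 0.83–0.93 under another. With visits tied to the calendar it was 0.96–1.00.

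**6. The outcome as written.** Section 3.2 scores Starting Phase samples by any week-over-week decrease. If Control is scored that way only in Weeks 1–4 (an assumption, since the article assigns Control no phases), the null OR was 1.9–3.2 on all samples and 2.1–3.2 on the 11 common weeks. Both favour CM, with 99–100% of null trials rejected.

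**The case against.** The best reply is that 11 assessments already means 11 common time points. Sections 3.2 and 3.5 give the number for a between-group comparison. Table 1 has a fixed-week treatment column (4, 8, 12, 16, 20, 26) with no distinction by arm, and all of those are Control weeks. Weekly CM visits would cover the calendar, and the image of Fig. 1, which I have not seen, may show it. On that reading the sampling bias disappears, as step 4 shows. So a reader should not infer that the plan pools every CM sample: it does not say so. Nor does it say the opposite. Table 1 puts PEth and uEtG under every visit, and a two-to-four-week interval does not place Sustaining visits on the Control weeks.

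Other parts of the reply also stand:
- The article names no working correlation, and with an exchangeable structure the bias is much smaller.
- If time is categorical and fully crossed with group, off-calendar CM samples under independence leave the contrasts at shared weeks unchanged.
- Weeks unsampled by schedule depend on observed PEth, so the methods in Section 3.4 could help. However, that section does not say they apply to visits that were never planned, and it does not address surplus samples.
- No calculation was made for uEtG. It shares the visits and so the mechanism, but its size is unknown.

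A condensed article may leave the mapping of visits to the full protocol or analysis plan. That does not cover when CM blood is drawn.

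**Conclusion.** The point holds in a limited form. The stated 11 equals the Control calendar. CM sampling depends on the outcome, and the article neither says which CM samples are analysed nor ties CM Sustaining visits to the Control weeks. If all CM samples are used with a <20 outcome, the null odds ratio falls to about 0.55–0.59 (independence) or 0.84–0.88 (exchangeable). Excessive drinking is distorted less, in the same direction. Restriction to Control weeks removes the bias only if CM visits fall there; otherwise what remains depends on the spacing. The all-sample direction for <20 follows from the visit rule; the sizes are illustrative and rest on the assumed PEth process and time coding.

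A reader might infer that the primary analysis as written is biased against CM and would hide a real benefit. The documents do not support that: the phase-dependent abstinence definition can push the result the other way, and by more. It is a separate problem, and the net direction depends on both.

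**What to change.** State in Section 3.2 that the treatment-period biomarker GEEs (PEth <20, PEth ≥200 and uEtG) use one sample per participant at the same 11 study weeks in both arms: 1–4, 6, 8, 12, 16, 20, 24 and 26. State in Section 2.3.2 that CM analysis samples are scheduled to include those weeks, and that all other CM samples serve reinforcement only. The two-to-four-week spacing already leaves room for this, and the reinforcement rules need not change.

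If this is not feasible, use one sample per common window, picked by a rule fixed in advance: Weeks 1–2, 3–4, 5–6, 7–8, 9–12, 13–16, 17–20, 21–24 and 25–26. That is nine windows instead of 11 weeks and leaves some bias (simulated null OR 1.13, 3% of null trials significant).

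The cost is some wording, scheduling of existing CM visits and at most a few extra kits; off-calendar CM samples leave the primary model. The abstinence definition needs its own correction, because common weeks do not cure it.
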